### Experimental diets

The HP-TDR and CON diets that will be consumed during both 32-h whole-body calorimetry conditions will be designed by a registered dietitian using the same approach as per the run-in diet. All food will be weighed and prepared by trained staff. Participants will receive three meals (breakfast, lunch, and dinner) and two snacks (afternoon and evening snacks) throughout each whole-body calorimetry test (Table 1). Bottled water will be provided *ad libitum.* The CON diet will provide 55% of total energy intake from carbohydrate, 15% from protein, and 30% from fat, and the HP-TDR diet will provide 35% of total energy intake from carbohydrate, 40% from protein and 25% from fat. Table 2 illustrates the nutrient composition of a typical 2000 kcal diet. The CON diet will be comprised of food items that can be found at the local grocery stores and the HP-TDR diet will consist of a soy-protein nutritional supplement (Almased®, Almased USA, Inc., St. Petersburg, FL, USA) mixed with olive oil and low-fat milk (1% fat) for the main meals and with olive oil and apple juice for the snacks, per label instructions [18]. The first dietary intervention randomly offered in the WBCU will be designed to maintain participants in energy balance and the energy content of each meal and snack will be identical for the HP-TDR and CON diets (eucaloric). Energy intake will be initially estimated using a 1-h RMR test, and it will be adjusted throughout the day on the basis of measured EE using WBCU data points. When the prescribed energy intake falls outside ±100 kcal of the predicted 24-h EE, the amount of calories provided in the dinner and evening snack will be adjusted (added or subtracted) in an attempt to achieve energy balance. Participants will be required to consume all the food provided and meal trays will be checked after consumption.

**Table 1 Tab1:** Composition of the CON and HP-TDR diets

Meals	CON Diet	HP-TDR
Breakfast	Whole wheat bread	HP-TDR powder
	Peanut butter	Low-fat (1%) milk
	Orange juice	Olive oil
	Low-fat (1%) milk^1^	
	Boiled egg^1^	
Lunch	Turkey wrap	HP-TDR powder
	*Flour tortilla*	Low-fat (1%) milk
	*Deli style turkey*	Olive oil
	*Cheese*	
	*Lettuce*	
	*Tomato*	
	*Olive oil*	
	Tomato soup	
	Canned peaches^1^	
	Yogurt^1^	
Afternoon snack	Apple	HP-TDR powder
	Crackers	Apple juice
	Cheese	Olive oil
	Yogurt^1^	
Dinner	Chicken stir fry	HP-TDR powder
	*Chicken breast*	Low-fat (1%) milk
	*Celery*	Olive oil
	*Carrot*	
	*Onion*	
	Brown rice	
	Yogurt^1^	
Evening snack	Cereal	HP-TDR powder
	Low-fat (1%) milk	Apple juice
	Almonds	Olive oil
	Canned peaches^1^	

^1^Food items added or not, depending on the energy requirements of the participants

Abbreviations: *CON* control, *HP-TDR* High-protein total diet replacement

**Table 2 Tab2:** Nutrient composition of a typical study diet

	HP-TDR	CON Diet
Energy		
*kcal/day*	2000	2000
Protein		
*g/day*	200	76
*% of TEI*	40	15
Fat		
*g/day*	55	67
*% of TEI*	25	30
Carbohydrate		
*g/day*	175	280
*% of TEI*	35	55

Abbreviations: *BW* body weight, *CON* control, *HP-TDR* high-protein total diet replacement, *TEI* total energy intake

### Appetite sensations

During each whole-body calorimetry condition, participants will rate their appetite sensations (hunger, satiety, fullness, and prospective food consumption) using a validated anchored 100-mm visual analog scale (VAS) [19]. Questionnaires will be administered using the paper-and-pen method, and participants will be instructed to make a single vertical mark at the appropriate point between the two anchors on each scale to indicate the intensity of their subjective states regarding each element. Participants will be asked to indicate, on a scale from 0 to 100 mm, how they feel at the moment they complete these questions: How hungry do you feel? (I am not hungry at all – I have never been more hungry); How satisfied do you feel? (I am completely empty – I cannot eat another bite); How full do you feel? (not at all full – totally full); How much do you think you can eat? (nothing at all – a lot). Participants will complete the questionnaires immediately before and 30 min after each meal (breakfast, lunch, and dinner) and snack (afternoon and evening). For each rating period, a new questionnaire will be provided to participants, and they will not be allowed to consult their previous ratings.

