### Experimental protocol

An outline of the experimental protocol is given in Fig. 1, and the schedule of enrollment, interventions, and assessments are provided in Fig. 2. Following the screening process, eligible participants will be invited to attend two study visits for a body composition assessment, a 1-h RMR test, and a fitness test. After these visits are complete, on separate intervention days, participants will undergo two 32-h whole-body calorimetry stays for the measurement of energy metabolism components, appetite sensations, and metabolic blood markers while consuming HP-TDR and CON isocaloric diets in a random order. A 3-day run-in period with a controlled, energy-balanced diet will precede both intervention phases. For women, each intervention phase will be followed by a wash-out period of approximately 1 month to preclude influences of the menstrual cycle. For men, a two-week wash-out period will be required to eliminate any effect of the diet. Participants will be instructed to maintain a stable body weight and physical activity level throughout the study period.

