### Whole-body calorimetry tests

On the day following the 3-day run-in periods, participants will return to the HNRU after fasting for 8 to 12 h and will spend 32 consecutive hours in the WBCU (8:00 am on day 1 until 4:00 pm on day 2) while receiving the HP-TDR and CON diets in a random order. On the morning of the tests, only minimal physical activity and voiding of the bladder will be requested of the participants before they enter the WBCU. Both 32-h whole-body calorimetry tests will happen during the follicular phase of the women’s menstrual cycles (i.e., between day 6 and 13) and will be conducted approximately 1 month apart (women) and 2 weeks apart (men). The whole-body calorimetry conditions will follow a strict and standard schedule (Additional file 2). Throughout each test, participants will receive three meals (at 9:00 am, 12:00 pm, and 6:00 pm) and two snacks (at 3:00 pm and 9:00 pm). Appetite sensations will be rated immediately before and 30 min after each meal and snack. Blood will be drawn four times (~ 7:30 am, 11:00 am and ~ 2:30 pm on day 1, and ~ 8:00 am on day 2), and urine will be collected for the entire time. On the morning of the first day of the test (10:20 am), a 40-min walking session on a treadmill (BH Fitness T8 SPORT, BH Fitness, Foothill Ranch, Calif., USA) will be completed, at a personalized fixed pace. Sleep will only be allowed during the night (from 10:00 pm to 6:00 am).

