### 24-h Energy expenditure and substrate oxidation

 24-h EE and macronutrient oxidation rates will be calculated from the measurements of VO_2_, VCO_2_, and excreted urinary nitrogen (N) by using the formula of Brouwer [17]:

$$ 24h\  EE\ \left( kcal/ day\right)=3.866\ x\  VO2\ \left(L/ day\right)+1.20\ x\  VCO2\ \left(L/ day\right)-1.43\ x\ N\ \left(g/ day\right) $$
$$ PROox\ \left(g/ day\right)=6.25\ x\ N\ \left(g/ day\right) $$
$$ CHOox\ \left(g/ day\right)=4.170\ x\  VCO2\ \left(L/ day\right)-2.965\ x\  VO2\ \left(L/ day\right)-0.390\ x\  PROox\ \left(g/ day\right) $$
$$ FATox\ \left(g/ day\right)=1.718\ x\  VO2\ \left(L/ day\right)-1.718\ x\  VCO2\ \left(L/ day\right)-0.315\ x\  PROox\ \left(g/ day\right) $$where PROox, CHOox, and FATox are the protein, carbohydrate, and fat oxidation rates, respectively, in grams per day. Energy and macronutrient balances will be calculated as the difference between intake and oxidation:

$$ Energy\ Balance= Energy\ Intake\ \left( kcal/ day\right)- Energy\ Expenditure\left( kcal/ day\right) $$
$$ Macronutrient\ Balance= Intake\ \left(g/ day\right)- Oxidized\ \left(g/ day\right) $$

The respiratory quotient will be calculated as the ratio of VCO_2_ exhaled to VO_2_ inhaled:

$$ RQ=\frac{VCO2\ (L)}{VO2\ (L)} $$

During each whole-body calorimetry test, the following components of participants’ energy expenditure will be assessed: 24-h EE, RMR, BMR (energy expended to maintain essential vital function), SMR, postprandial EE, and exercise EE. The RMR will be assessed as described above. The BMR will be assessed in the morning of the second day of the test. Participants will receive a wake-up call at 6:00 am and will be instructed not to get up from bed but to rest in a supine position while awake but motionless for 60 min. The SMR will be computed for a 3-h period (2:00 am to 5:00 am), and the sleep EE will be extrapolated to an 8-h sleep night. Postprandial EE will be assessed on the second day of the test for the 6 consecutive h after the participants have finished their breakfasts. Exercise EE will be assessed in the morning of the first day of the test for 40 min during the exercise session (10:20 am to 11:00 am).

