#### Data analysis

IBM® SPSS® Statistics version 24 (International Business Machines Corporation, New York, NJ, USA) will be used to perform statistical analyses. Differences will be regarded as statistically significant if *p* < 0.05. Missing data will be omitted, and the remaining data will be analyzed. To determine whether a statistically significant mean difference exists between the HP-TDR and CON groups, a paired-samples t-test or Wilcoxon signed rank test will be used, depending on the data distribution. Shapiro Wilk’s test will be used to check the normality of the data. Inspection of a boxplot for values greater than 1.5 box-lengths from the edge of the box will be done to detect outliers. A two-way repeated measures analysis of variance (ANOVA) will be carried out to determine the effect of the dietary interventions on appetite sensations. Outliers will be detected by studentized residuals greater than ±3 standard deviations. Sphericity will be assessed for the interaction term by the Mauchly’s test of sphericity. The relationships between variables will be determined by a Pearson’s product-moment correlation. To determine whether the order of treatment has an effect on the results, a repeated measures ANOVA with the order of treatment as the between-subjects factor will be performed.

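### The appetite analysis sets no baseline apart, so read literally a rating made before any test food enters the diet main effect as an ordinary time point

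*Protocol article*

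**What the plan says.** All references are to the protocol article.

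- **Ratings.** The section Appetite sensations assigns them to the stay as a whole: "During each whole-body calorimetry condition, participants will rate their appetite sensations (hunger, satiety, fullness, and prospective food consumption"). On timing it says "Participants will complete the questionnaires immediately before and 30 min after each meal (breakfast, lunch, and dinner) and snack (afternoon and evening"). No rating is called a baseline.
- **Meals.** Under Whole-body calorimetry tests, "participants will receive three meals (at 9:00 am, 12:00 pm, and 6:00 pm) and two snacks (at 3:00 pm and 9:00 pm").
- **State on entry.** The same section says "participants will return to the HNRU after fasting for 8 to 12 h and will spend 32 consecutive hours in the WBCU", entering at 8:00 am. Under Experimental protocol, "A 3-day run-in period with a controlled, energy-balanced diet will precede both intervention phases".
- **Outcome.** Outcome measures lists appetite among the exploratory outcomes, as a difference between the two conditions. The blood markers in the same list are defined as a change in concentration, and Blood and urine analysis labels their first draw as baseline.
- **Model.** Under Data analysis, "A two-way repeated measures analysis of variance (ANOVA) will be carried out to determine the effect of the dietary interventions on appetite sensations", and "Sphericity will be assessed for the interaction term by the Mauchly’s test of sphericity". No covariate, change score or omitted rating is mentioned for appetite.

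**The concern.** A rating made before the first test meal can carry no effect of that meal plan. Averaged into the diet main effect, it contributes zero signal and its own chance variation between two visits 2 weeks apart (men) or about a month apart (women). It thus pulls the estimated diet effect towards zero.

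The same rating would be useful as a baseline. If a participant arrives hungrier at one stay than at the other and this persists through the day, the difference is carried into the diet comparison. The trial records the value that could adjust for it. The article sets up a per-stay baseline for the blood markers but not for appetite, although appetite is part of the stated aim and the Discussion hypothesises greater satiety on the high-protein diet.

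**Working it through.** The article gives no effect size, standard deviation or correlation for the appetite scales, so there is no planned figure to reproduce. The attenuation is plain arithmetic. The power figures rest on assumptions and are shown as a range.

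**1. Number of ratings, K.** Three meals and two snacks, each rated twice: K = 5 × 2 = 10 per scale and stay. The section on 24-h energy expenditure implies a second breakfast: "Postprandial EE will be assessed on the second day of the test for the 6 consecutive h after the participants have finished their breakfasts". If that breakfast is also rated (an assumption), K = 6 × 2 = 12.

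**2. Ratings before exposure.** The unit is entered fasted at 8:00 am and the first test meal is at 9:00 am. Exactly one rating, the first, precedes all test food.

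**3. Diet main effect.** In a diet-by-time ANOVA the main effect is the between-diet difference averaged over the K ratings. With zero effect at the first rating and a constant effect D at the others:

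- main effect = (0 + (K − 1)D)/K
- K = 10: 0.900 D, a loss of 10.0%
- K = 12: 11/12 = 0.917 D, a loss of 8.3%

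**4. Precision.** Let each between-stay difference have variance σ², and let ρ be the correlation between these differences at two ratings of the same participant. The variance of the average of m ratings is σ²[ρ + (1 − ρ)/m]. Including the first rating lowers this variance slightly, but by less than it lowers the signal. The ratio of signal to standard error, all ratings against later ratings only, is

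((K − 1)/K) × √{[ρ + (1 − ρ)/(K − 1)] / [ρ + (1 − ρ)/K]}

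- K = 10, ρ = 0.1: 0.9 × √(0.200/0.190) = 0.923
- K = 10, ρ = 0.6: 0.9 × √(0.6444/0.640) = 0.903
- K = 12, ρ = 0.1: 0.917 × √(0.1818/0.175) = 0.934

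**5. Power.** Simulation of paired differences, 20,000 runs per setting, K = 10 or 12, n = 12 or 19 (numbers taken from Sample size estimate), two-sided 5% level. The effect was set so that the test on the later ratings alone has noncentrality 3.0. Values of ρ are assumed. Ranges are over K and n.

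| ρ | All ratings | Later ratings only | Later ratings, baseline covariate | Change from baseline |
|---|---|---|---|---|
| 0.1 | 71.3–75.4% | 77.9–81.1% | 75.3–80.8% | 21.9–24.1% |
| 0.3 | 70.6–75.0% | 78.0–81.8% | 83.8–88.8% | 47.6–50.4% |
| 0.6 | 69.4–73.9% | 78.0–81.3% | 96.8–98.5% | 90.6–92.5% |

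Keeping the first rating costs about 5 to 9 percentage points against dropping it. The covariate brings nothing at ρ = 0.1 (up to 2.6 points lower than dropping the rating), about 6 to 7 points at 0.3 and 17 to 19 at 0.6. The raw change score is far worse at low and moderate ρ.

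**6. Interaction.** With K = 10 the diet differences over time are 0, D, …, D. Their mean is 0.9 D, and the sum of squares about it is (0.9 D)² + 9 × (0.1 D)² = 0.90 D². A diet effect that is perfectly uniform after breakfast thus produces a diet-by-time interaction, spread over (2 − 1)(10 − 1) = 9 degrees of freedom. A significant interaction would not tell the reader whether the effect varies over the day or merely differs from the pre-diet state.

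**The case against.** The strongest objection is that a collection schedule is not an analysis set. The article says when questionnaires are filled in and which model is used, but not which ratings enter it. A condensed article may leave that to the full protocol or the SAP, neither of which is shown. This stands: a reader might infer that the plan expressly counts the pre-breakfast rating as a response to diet, and the article does not say so. What remains is that the stated outcome form and model, followed as written, put the rating in, and nothing takes it out.

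A reader might also infer that each stay's baseline goes unused. That does not hold if time is the second factor, as the planned interaction term suggests. The interaction compares the diet difference at the first rating with those later, so equal starts followed by divergence are part of what it detects. It does not, however, repair the main effect, and step 6 shows that its meaning becomes mixed.

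Third, diet order is randomised, so a chance difference in fasting appetite is noise and not bias, and its direct weight in the average is only 1/10 or 1/12. This is correct. The attenuation is towards no effect.

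Fourth, the covariate is not uniformly better than simply dropping the rating. This also stands, as the row for ρ = 0.1 shows.

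**Conclusion.** The point holds as a modest improvement to one exploratory outcome. On the literal reading, the diet main effect for appetite is attenuated by 10.0% with 10 ratings or 8.3% with 12. This assumes a constant effect after the first test meal and none before it (so no effect of anticipating the coming diet). If the later effect varies over the day, the same fraction applies to its average. The power loss of about 5 to 9 points depends further on the assumed correlations and effect size.

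It would go too far to conclude that the appetite results would be biased in favour of either diet, or that the trial's main conclusions are affected. Fat balance, 24-h energy expenditure and the sample size do not depend on these ratings.

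**What to change.** State in the analysis section that:

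- the day-1 pre-breakfast rating is the baseline of that stay and is not a level of the time factor;
- the outcome is formed by the later ratings (9, or 11 if a day-2 breakfast is rated);
- the diet effect is adjusted for the stay's own baseline, either in a mixed model with baseline as a covariate that varies between stays, or by regressing each participant's mean paired difference on the baseline difference. In the regression the diet effect is the intercept at a baseline difference of zero, so the baseline difference must not be mean-centred;
- change from baseline is not the main analysis.

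The data are already collected and participants do nothing extra. The costs are one degree of freedom, little or no gain over merely dropping the rating if the within-stay correlation is low (the article does not give it), and a change of model, since a standard repeated measures ANOVA takes one covariate value per participant and not one per stay. If that change is unwanted, leaving the first rating out of the time factor already removes the attenuation.

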### Blood and urine analysis

Blood will be sampled by venipuncture from participants at four time points during each whole-body calorimetry condition: 1) the morning on the first day of the test (Baseline); 2) immediately after the exercise session (4 h post-baseline); 3) two hours after lunch (7.5 h post-baseline); and 4) the morning on the second day of test (24 h post-baseline). Both morning blood draws will be sampled from subjects after a 10-h overnight fast. Blood will be drawn into BD Vacutainer® blood collection tubes (Becton, Dickinson and Company, Franklin Lakes, NJ, USA), spray-coated with silica and a polymer gel for serum separation or with K_2_-ethylenediaminetetraacetic acid (EDTA) for plasma separation. Before centrifugation, a protease inhibitor 4-(2-aminoethyl)benzenesulfonyl fluoride hydrochloride (AEBSF) (Sigma-Aldrich, Oakville, ON, Canada) will be added to the K_2-_EDTA tubes. Samples will be centrifuged at 450 xg for 10 min and aliquoted for storage at −80 °C for the subsequent measurement of biomarkers. Hydrochloric acid (1 N, 100 μL) will be added to the ghrelin aliquot prior to storage. Serum samples will be analyzed for glucose, insulin, cholesterol, HDL cholesterol, LDL cholesterol, triglyceride, and non-HDL cholesterol by DynaLIFE Medical Labs (Edmonton, AB, Canada). Plasma samples will be analyzed for ghrelin, PYY, GLP-1, leptin, free glycerol and non-esterified fatty acids (NEFA) at the HNRU (University of Alberta, Edmonton, AB, Canada). Leptin and GLP-1 (active) will be measured by electrochemiluminescence using the MULTI-ARRAY® Assay System (Meso Scale Discovery®, Gaithersburg, Md., USA) and V-PLEX® (Meso Scale Discovery®, Gaithersburg, Md., USA), respectively. Ghrelin (active) and PYY will be measured using enzyme-linked immunosorbent assay (ELISA) kits from EMD Millipore Co. (Billerica, Mass., USA). Free glycerol and NEFA will be measured using enzyme immunoassay kits from Zen-Bio Inc. (Research Triangle Park, N.C., USA).

Urine will be collected for the entire time from the participants while at the WBCU for the measurement of urinary N. Collections will be initiated after the first morning urinary void and collected into sterile urine jugs. During collection, urine will be stored at −1 °C inside a refrigerator located in the WBCU and will be taken to the laboratory after each whole-body calorimetry test ends. Urine volume will be measured, and aliquots (~ 1.5 mL each) will be placed into tubes for storage at −80 °C before analysis. Total urinary N will be determined by chemiluminescence using a high temperature Shimadzu TOC-L CPH Model Total Organic Carbon Analyzer with an ASI-L autosampler and TNM-L unit (Shimadzu Corporation, October 2015. Suzhuo, Jiangsu, China).

#### Data analysis

IBM® SPSS® Statistics version 24 (International Business Machines Corporation, New York, NJ, USA) will be used to perform statistical analyses. Differences will be regarded as statistically significant if *p* < 0.05. Missing data will be omitted, and the remaining data will be analyzed. To determine whether a statistically significant mean difference exists between the HP-TDR and CON groups, a paired-samples t-test or Wilcoxon signed rank test will be used, depending on the data distribution. Shapiro Wilk’s test will be used to check the normality of the data. Inspection of a boxplot for values greater than 1.5 box-lengths from the edge of the box will be done to detect outliers. A two-way repeated measures analysis of variance (ANOVA) will be carried out to determine the effect of the dietary interventions on appetite sensations. Outliers will be detected by studentized residuals greater than ±3 standard deviations. Sphericity will be assessed for the interaction term by the Mauchly’s test of sphericity. The relationships between variables will be determined by a Pearson’s product-moment correlation. To determine whether the order of treatment has an effect on the results, a repeated measures ANOVA with the order of treatment as the between-subjects factor will be performed.

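### Repeated-measures ANOVA plus omission of missing data means one missed mark out of 20 removes a participant from that appetite scale's analysis; a mixed model on all available ratings avoids this

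*Protocol article*

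**What the plan says.** The Data analysis section of the protocol article fixes the method for appetite: "A two-way repeated measures analysis of variance (ANOVA) will be carried out to determine the effect of the dietary interventions on appetite sensations". It adds a check on that model, "Sphericity will be assessed for the interaction term", by Mauchly's test, and names SPSS version 24 as the software. The same section has one missing-data rule for all outcomes: "Missing data will be omitted, and the remaining data will be analyzed".

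The rating schedule is in the Appetite sensations section: "Participants will complete the questionnaires immediately before and 30 min after each meal (breakfast, lunch, and dinner) and snack (afternoon and evening"). Collection is on paper: "Questionnaires will be administered using the paper-and-pen method". The Whole-body calorimetry tests section lists three meals and two snacks per test. Under Experimental protocol, "participants will undergo two 32-h whole-body calorimetry stays", one on each diet. The Outcome measures section lists appetite sensations among the exploratory outcomes.

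**The concern.** A classical two-way within-subject ANOVA works on a complete diet-by-time table for each person. It cannot use a person with an empty cell. Under this method, omitting a missing value therefore means omitting all of that person's ratings on that scale, including the 19 that were recorded.

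The article fixes both the rule and the method, so this is not a detail left open for a fuller document. With samples this small, the loss of a few participants costs power and limits the appetite result to people with perfect records. The planned sphericity check is exposed as well, because it needs a minimum number of complete participants.

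**Working it through.** **Inputs from the protocol article**

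- Eating occasions per stay: 3 meals + 2 snacks = 5.
- Ratings per occasion: 2 (just before and 30 min after).
- Stays per participant: 2.
- Sample size per sex: 12, on the respiratory quotient calculation. I also use 19, the per-arm figure in the alternative fat-balance calculation, as a larger case.

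The article states no power or missing rate for appetite, so there is no appetite figure to reproduce. The power figure that goes with N = 12 does reproduce. With difference 0.06 against null 0.05 and SD of the paired difference 0.01, the noncentrality is (0.01/0.01) × √12 = 3.46. Power is 88.3% with 11 degrees of freedom and 87.6% with 10, against 88% stated.

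**Cells per scale**

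5 × 2 = 10 ratings per stay, and 10 × 2 = 20 per participant. This reads the two factors as diet and time, with each rating a time level. Twenty is the lower count: "Postprandial EE will be assessed on the second day of the test", following a breakfast that day. If that meal is rated too, the count is 12 × 2 = 24.

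**Participants lost**

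Assume each mark is missed independently with probability p. The chance of at least one miss is 1 − (1 − p)^20, and the expected number of complete participants is N(1 − p)^20.

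| p (assumed) | (1 − p)^20 | Lost per scale | Complete of 12 | Complete of 19 |
|---|---|---|---|---|
| 0.5% | 0.905 | 9.5% | 10.9 | 17.2 |
| 1% | 0.818 | 18.2% | 9.8 | 15.5 |
| 2% | 0.668 | 33.2% | 8.0 | 12.7 |
| 5% | 0.358 | 64.2% | 4.3 | 6.8 |

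**If misses cluster within people**

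With a beta-binomial model and an assumed within-person correlation of 0.3, the share with at least one miss falls to 5.6%, 10.9% and 25% at p = 1%, 2% and 5%.

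**Power for the diet main effect**

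Take an effect with 80% power on complete data (standardised paired difference 0.889 at N = 12, 0.680 at N = 19). Average the paired-t power over the binomial number of complete participants, with independent misses.

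| p | N = 12 | N = 19 |
|---|---|---|
| 1% | 69% | 70% |
| 2% | 57% | 60% |
| 5% | 26% | 32% |

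A simulation that keeps every available mark stayed at about 79% to 81% at each rate. It used a paired test on time-adjusted participant means as a stand-in for a mixed model. The assumed SDs were 12 between participants, 8 participant-by-diet and 12 residual.

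**Sphericity check**

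Two diets by 10 times give 1 × 9 = 9 interaction contrasts. Mauchly's test needs a non-singular 9 × 9 covariance matrix, hence at least 10 complete participants. At N = 12 it cannot be computed once three people are lost (12 − 3 = 9).

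**Which mixed model**

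The ten ratings within a stay share a participant-by-diet effect. I simulated no true diet effect with the same SDs. A model with only a random participant intercept rejected about 35% of the time at both N = 12 and N = 19, against a nominal 5%. A paired comparison of participant means held 5%.

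**The case against.** The strongest reply is that the loss may be small. Ratings are taken in an inpatient unit on a strict schedule with staff nearby, no document gives a missing rate, and misses may cluster in a few people. All of this stands. It lowers the expected loss, as the clustered figures show, and with no missed marks the loss is zero. It does not change the fact that the stated rule and method discard valid ratings whenever a mark is missed.

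A second reply is that the article never says cases are deleted whole. That is true, but the named ANOVA has no other way to handle an empty cell, and the Mauchly check indicates that the classical procedure is meant.

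A third reply is that appetite is exploratory. This limits the importance of the point.

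A reader might go further and infer that the 13 blood markers, drawn four times per stay, are left to within-diet comparisons with baseline and 13 × 4 = 52 separate tests. The documents do not support that. The Data analysis section names a paired t-test or signed-rank test between diets, and the Outcome measures section defines the marker outcome as change over time and between conditions. A paired test on each person's change from baseline satisfies both and compares the diets directly. The count of 52 also treats the pre-diet draw as a diet test. How the four times are modelled is a detail that an article may leave to the full protocol.

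**Conclusion.** The point holds for the appetite scales. One missed mark in 20 removes a participant from that scale's ANOVA. The loss is 9.5% to 64% of participants per scale for independent miss rates of 0.5% to 5%, less under clustering and none with complete data. The structural fact follows from the article, taking diet and time as the two factors; the size rests on assumed miss rates. The power figures also assume an effect with 80% power on complete data.

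The consequence is confined to exploratory outcomes. Fat balance and 24-h energy expenditure have one value per stay and do not go through this ANOVA. The point does not extend to a claim that the plan prescribes faulty inference for the blood markers.

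**What to change.** Replace the appetite ANOVA with a linear mixed model for each scale, fitted by REML to all available ratings:

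- fixed effects: diet, time, diet × time, period and sequence;
- random effects: participant and participant-by-diet, or an equivalent within-stay covariance;
- degrees of freedom: Satterthwaite or Kenward-Roger, as the software version allows;
- inference: the average diet contrast and the diet × time contrast.

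State that a random participant intercept alone will not be used. Restrict the omission rule so that it drops the missing rating, not the person.

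The same model form can serve the blood markers, with each stay's pre-diet sample as baseline and inference from the between-diet contrast. That is an option for consistency, not the repair of an error.

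The cost is a change of analysis text; the stated package has a mixed-model procedure. A covariance structure must be chosen in advance, and the analysis assumes that data are missing at random. It does not address multiplicity across the scales.
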